#### Patient Recruitment Strategy and Consent

Shortly before attending the Launch Workshop, the healthcare providers will identify potential eligible patients for the HMI Beta Phase, based on identified inclusion and exclusion criteria. Each full time equivalent rostering physician and nurse practitioner is requested to recruit a minimum of 100 patients and up to a maximum of 200 patients. A patient friendly consent form has been developed and will be signed by each participant. Copies of the consent, an accompanying script and other materials will be provided to each participating office. In addition to these documents, an implementation guide will also be provided to each site. (Thorough explanations of the materials will also be provided by Heart and Stroke Outreach and Practice Support Specialists at 'on site' visits.)

Appointments with the potential eligible patients will be scheduled to occur subsequent to the workshop with the participating practitioners. During this visit, these potential eligible patients will be provided with information about the HMI Beta Phase, patient consent will be requested and documented and a baseline assessment including physical measures conducted and documented. When a patient provides consent, (s)he is deemed to have enrolled in the HMI Beta Phase. Ethics approval has been obtained from the Sunnybrook Health Sciences Centre Research Ethics Board (approval #: 474-2006).

Utilizing adult learning best practices, the format of the site initiation Launch Workshop is one in which physicians, pharmacists and nurses will learn together and discuss barriers and solutions to better manage hypertension together and via small group breakout sessions, develop a community practice plan to improve the management and control of hypertension among their patients. The purposes of this interactive, inter-professional workshop include addressing any knowledge gaps identified in the healthcare provider needs assessment, introducing concepts of systems change theory and related applications, and developing approaches to high blood pressure based on inter-professional teamwork. This will be accomplished by providing information/education on best practices in management of hypertension, and a tool kit of supporting practice and behaviour change tools to all participating healthcare providers.

#### Implementation of Toolkit and Interventions

When a patient provides consent, (s)he is deemed to have enrolled in the HMI Beta Phase. Only then will his/her baseline data collected on the registration (baseline) visit data form designed as a flow sheet, be entered into the web-based dataset, using a unique ID to ensure that the web-based dataset is anonymized and pseudonymized. A flow sheet form will continue to be used during the subsequent patient visits. The flow sheets will become a part of the patient's chart. At the time of use, the flow sheet will graphically show the trends from all earlier visits in several key variables including systolic/diastolic blood pressure, BMI/waist circumference, lipids and lifestyle goal variables.

At the time of recruitment, the sites in this initiative were divided almost 50-50 in the use of either paper or electronic medical record (EMR) for clinical/patient record documentation. Existing EMR systems at the sites are unable to systematically and fully capture and subsequently extract and upload the patient data required for this project. Therefore, each participating EMR vendor has undertaken to create and insert into their system a "data collection template screen" specifically customized to capture and export the data set requirements of this project. After a patient has consented, a copy of the patient information needed for this strategy is exported from the practitioner's EMR and transferred securely into the project's central, securely housed clinical data repository ("web-based dataset"). Specifically, the data will be formatted in a standardized project-specific format as an XML file, along with enforcement of XSD-based validity checks, and transmitted to the web-based data set via HTTPS (encrypted HTTP) using a SOAP-based web service provided by the database host. The aforementioned encryption will prevent access to patient information while it is in transit. For electronic medical record (EMR) sites, the data will automatically be exported once nightly in a standardized format from the site's EMR to the web-based dataset.

For paper-based sites, the initial paper flow sheet is provided to each healthcare provider with a paper based clinical record documentation system. Follow up visit paper flow sheets are obtained by downloading the follow-up visit form from the website shortly before every follow-up visit, i.e. after the prior visit's data have been processed and incorporated into the updated data graphs. Two methods are available for transferring the data from the paper forms to the web-based data set. In the first method, at the end of each visit, the flow sheet will be faxed by toll-free number to the data centre for optical scanning and aggregation into the web-based data set. To insure data accuracy, the scanned information will be validated by a human operator at the centre and corrected for errors. The faxed form will include neither the name of the patient nor any other identifying information such as address or phone number. This is possible because each patient will be assigned a unique sequential identifier by the practitioner's office at the time of the baseline (registration) visit, the identifier being pre-printed on the practitioner's pad of blank Registration visit forms. The practitioner's office will subsequently supply the patient's name directly into the web-based dataset by matching with the anonymous identifier and birthdate. This procedure facilitates the subsequent downloading of each patient's own follow-up forms containing their pre-printed data graphs, whose ongoing feedback is an important component to promoting the success of the project. In the second method, at the end of each visit, the data from the flow sheet will be manually entered into a secure website directly linked to the web-based data set.

After patient information is entered into the dataset, monthly and quarterly confidential practice audit reports will be available to all practitioners on the secure website linked to the web-based dataset. Moreover, the practitioner will be able to access the data set at anytime and generate ad hoc "drill-down" reports on his/her patients only. While the same practitioner can compare aggregate data from different sites, he/she cannot access the individual patient information of another physician. The web-based dataset will generate regular confidential practice reports based on the data submitted, for each participating physician and nurse practitioner, comparing the practice to that of other providers at the same site and to those of the other sites and participating healthcare providers. Reports are also generated at a site level for the other healthcare providers to access.

The web-based dataset will be hosted on a Personal Health Information Protection Act (PHIPA) compliant server provided by the dataset developer.

The patient will also be offered the patient toolkit, including the "Take the Pressure Off" patient book. This patient resource provides information and education on hypertension, its risk factors, lifestyle change information, and lists other resources. The Patient-Provider Agreement will be reviewed and completed, including the BP goal, the patient's selected lifestyle risk factor which (s)he wishes to focus on in the coming months/years and the patient's personal plan of action for this selected lifestyle risk factor. The Patient-Provider Agreement is incorporated into the "Take The Pressure Off". The BP goal and patient selected lifestyle risk factor is also documented in the HBP Registration (baseline) and Flow sheet (follow-up) data forms.

In order to assess the impact of the Hypertension Management Initiative on both healthcare provider practice patterns and patient blood pressure readings and control, it is necessary to compare data from the pre-program period to the program period. In order to assess any changes from before to after the intervention, a combination of chart reviews, for the pre-program period, and the web-based patient dataset, for the program period, will be used. Thus, data about the practice patterns of individual healthcare providers and their individual patients' blood pressure data will be used as their own comparators pre-intervention versus post-intervention.

Given that HSFO approached this particular group of health care providers to participate in a program relating to hypertension, this may have heightened their awareness of the issue and affected their management of patients with hypertension (in addition to the influence of the intervention itself). This phenomenon in which subjects of research may be affected by the knowledge that they are subjects of research is known as the Hawthorne Effect. For this reason, data will be collected from both the immediate intervention and delayed intervention groups pertaining to office visits conducted during the six months prior to initial contact with sites for recruitment into the initiative as well as data from office visits after first contact but before the site initiation workshop. Gathering this data will allow an assessment of practice patterns for these groups between the pre-recruitment period and the period following recruitment, which may relate to the Hawthorne Effect. As well, this will allow comparisons to be made between the immediate intervention and delayed intervention groups in terms of patient blood pressure readings as well as healthcare provider practice patterns.

In the patient consent form, patients are informed that information from their medical chart may be collected in order to evaluate the education and tools provided to themselves and their health care provider, and that all information collected would be kept strictly confidential and would be grouped for analysis. All participating and nurse practitioners have provided written consent to a chart review with the intent to evaluate the education and tools provided to the healthcare providers.

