**Immediate Intervention**	*Measurement:* • BP readings (sphygmom.) • site characteristics • practice patterns re. HTN management	*Receive intervention*: • workshop • tools enrolment of patients *Measurement*: • baseline BP readings (BpTRU)	(continue to receive site support for intervention) *Measurement*: • follow up visit • BP readings (BpTRU)	(continue to receive site support for intervention) *Measurement:* • follow up visit • BP readings (BpTRU)	*Measurement:* • follow up visit • BP readings (BpTRU) • practice patterns re. HTN management

**Delayed Intervention**	*Measurement*: • BP readings (sphygmom.) • site characteristics • practice patterns re. HTN management	treatment as usual	*receive intervention:* • workshop • tools enrolment of patients *measurement*: • baseline BP readings (BpTRU)	(continue to receive site support for intervention) *Measurement:* • follow up visit • BP readings (BpTRU)	*Measurement:* • follow up visit • BP readings (BpTRU) • practice patterns re. HTN management

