**Figure 2 F2:**
[figure not shown]
**Rx Dx Prescription**.

An office automated blood pressure monitor, the BpTRU, is provided to each family physician and nurse practitioner. The BpTRU monitor is to be used to take the blood pressure reading [6]. As data from each healthcare provider (physicians and nurse practitioners) is inputted in the web based data set, confidential practice audit reports will be produced for each healthcare provider. The HMI's supporting practice and behavior change tools that are to be integrated into practice will be presented during the Launch Workshop.

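### The chart-review versus web-dataset comparison of blood pressure changes device when the program starts, so any device offset is counted as program effect in that comparison

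*Protocol article*

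**What the plan says.** The last part of Implementation of Toolkit and Interventions (Protocol article) sets out how impact on provider practice and on patients' BP readings and control will be judged. It holds that "it is necessary to compare data from the pre-program period to the program period", and that for this purpose "a combination of chart reviews, for the pre-program period, and the web-based patient dataset, for the program period, will be used". It adds that "individual patients' blood pressure data will be used as their own comparators pre-intervention versus post-intervention".

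That section names no device. Table 3 (Rationale for the Evaluation Design) does. The Time 1 entry for both groups is "BP readings (sphygmom", abbreviated for sphygmomanometer. The enrolment entry, at Time 2 for the immediate group and Time 3 for the delayed group, is "baseline BP readings (BpTRU", and every later BP entry is also BpTRU.

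The program brings the new device with it. The BpTRU is listed in the provider toolkit (Table 6), and the text after Figure 2 says: "An office automated blood pressure monitor, the BpTRU, is provided to each family physician and nurse practitioner". The web dataset starts at the registration visit, once consent is given: "Only then will his/her baseline data collected on the registration (baseline) visit data form" be entered.

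The article also describes two other BP comparisons. The Abstract (Methods) compares baseline with annual measurements within all subjects. The Abstract and Rationale for the Evaluation Design compare the immediate group's follow-up with the delayed group's baseline at Time 3.

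**The concern.** A before-after comparison attributes to the program whatever changes at the boundary between before and after. Here the measuring instrument and the way readings are recorded change at that boundary, for every patient in both groups. If the two methods differ systematically, mean BP moves by that difference even if no patient's true BP has changed. The proportion controlled to target moves as well, because it is defined by a threshold on the same readings. Table 2 lists both as key indicators.

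The article gives no paired readings, conversion, adjustment for device or caveat for this comparison. A larger sample does not help: it narrows the interval around a biased value.

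**Working it through.** **Step 1. Match the device to each side of each BP comparison.**

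| Comparison | Where stated | First reading | Second reading |
|---|---|---|---|
| Pre-program versus program, within patient | Implementation of Toolkit and Interventions | Chart review; sphygmomanometer at Time 1 (Table 3) | Web dataset; BpTRU |
| Enrolment versus annual, within patient | Abstract, Methods | BpTRU | BpTRU |
| Immediate follow-up versus delayed baseline, Time 3 | Abstract, Methods; Rationale for the Evaluation Design | BpTRU | BpTRU |

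Only the first row changes device. One inference is needed: that the chart BP of the pre-program period is the Time 1 BP of Table 3. Time 1 is the only pre-program BP measurement in that table.

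**Step 2. Find a scale from the plan's own figures.** Statistical Design and Analysis gives a difference of 5 mmHg, alpha 0.05, two-sided tests and 337 per group. It gives no SD. It states both power 0.9 and beta 0.20, which disagree with each other; that is a separate matter, so both are tried here.

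- n per group = 2 × (z for alpha + z for power)² × SD² / 5².
- Power 0.90, SD 20: 2 × (1.960 + 1.282)² × 400 / 25 = 336.2, rounded up to 337.
- Power 0.80: 337 is reproduced by an SD of about 23.2.

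An SD of 20 mmHg is therefore consistent with the plan, but it is an assumption.

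**Step 3. Find the offset that would be significant with zero true effect.** Assumptions: SD 20 at each time, within-patient correlation 0.5, independent patients, and a usable chart reading for each.

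- SD of the paired change = 20 × √(2 × (1 − 0.5)) = 20 mmHg.
- At the enrolment goal of 5,000: SE = 20 / √5,000 = 0.283, and 1.96 × 0.283 = 0.55 mmHg.
- At 337: SE = 20 / √337 = 1.09, and 1.96 × 1.09 = 2.1 mmHg.

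Range over other assumed SDs of the paired change:

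| SD of change (mmHg) | Threshold, n = 5,000 | Threshold, n = 337 |
|---|---|---|
| 15 (SD 20, correlation about 0.72) | 0.42 | 1.6 |
| 20 (SD 20, correlation 0.5) | 0.55 | 2.1 |
| 23.2 (SD 23.2, correlation 0.5) | 0.64 | 2.5 |

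**Step 4. Probability of a significant result from the offset alone** (two-sided 5% test, SD of change 15 to 20, independent patients):

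| Assumed offset | Share of the 5 mmHg design difference | n = 337 | n = 5,000 |
|---|---|---|---|
| 1 mmHg | 20% | 0.15 to 0.23 | 0.94 or more |
| 2 mmHg | 40% | 0.45 to 0.69 | about 1 |
| 3 mmHg | 60% | 0.79 to 0.96 | about 1 |
| 5 mmHg | 100% | above 0.99 | about 1 |

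Patients are clustered in 11 sites. Allowing for this would widen the SEs and raise the thresholds. It would not change the expected bias, which equals the offset.

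**The case against.** The strongest reply is that the comparisons the Abstract relies on do not have this fault. The enrolment-to-annual analysis and the Time 3 comparison are BpTRU on both sides. This stands, and it limits the point to one comparison. It does not rescue that comparison, which the article calls necessary for judging impact on BP and does not mark as exploratory.

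A second reply is that each patient also has an enrolment BpTRU reading, which lies between the chart reading and follow-up and so helps to separate the change of device from later change. This is partly right, and the fix uses it. But the comparison as written sets chart data against the web dataset, and the enrolment reading is already in the web dataset.

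A third is that the BpTRU is part of the intervention. Even so, a change of instrument can alter recorded BP without altering true BP, and the stated aim is control of BP.

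A fourth is that handling of the device may be left to a fuller document. The article itself, however, fixes the two data sources and the own-comparator use, so this is a stated choice and not an omitted detail.

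A last reply concerns the figures: the SD, correlation and independence are assumed, and nothing says that all 5,000 patients will have a usable chart BP. This stands. The figures show scale only.

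**Conclusion.** The point holds for the within-patient comparison of chart review with the web dataset. There, device and recording method are aliased with the start of the program. The bias is structural; its size and direction cannot be found in the documents. Under the assumptions in step 3, an offset of about 0.55 mmHg (5,000 patients) or 2.1 mmHg (337) would be significant with no true effect, that is about 11% or 43% of the 5 mmHg design difference.

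A reader might infer more, and the documents do not support it:

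- *The trial's BP results as a whole are invalid.* The other two BP comparisons use one device throughout.
- *The bias favours the program.* No direction is given; it could equally hide an effect.
- *The setting of measurement changes too.* The chart data come from office visits, and the BpTRU is described as an office monitor.
- *The offset drops out of a between-group difference of changes from Time 1 to Time 3.* It does so only if it is similar in both groups. Sites are assigned manually, and at Time 3 the immediate group has used the BpTRU for nine months while the delayed group is giving its first BpTRU readings.

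**What to change.** Change the end of Implementation of Toolkit and Interventions as follows:

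1. Within-patient effects on BP and BP control use BpTRU readings only, enrolment versus follow-up, in line with the Abstract.
2. Chart review is kept for provider practice patterns.
3. Within-group change from chart BP to BpTRU is reported, if at all, as descriptive and confounded by device.
4. Time 1 BP may be used to compare the groups before the program. It may also enter a supportive between-group difference of changes to Time 3, with the assumption of a similar device offset in both groups stated. That difference of changes would be an added analysis.

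The first three are changes of text and need no new data. The real cost is in what is estimated. Enrolment visits follow the provider workshop (Patient Recruitment Strategy and Consent), so the enrolment reading is not strictly pre-intervention. Any change between the workshop and enrolment is left out of the within-patient estimate, and the article should say so.

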### Key Objectives of HMI – Beta Phase

The HMI Beta Phase is designed to improve patient outcomes with respect to the control of blood pressure. There are two key elements to the initiative. Firstly, it is designed to improve provider practices and management of essential hypertension. Secondly, it is designed to improve provider-patient interactions and patient self-management of hypertension.

The HMI Beta Phase will achieve these objectives by incorporating various strategies, including inter-professional education, practice outreach and facilitation, an inter-professional healthcare provider toolkit and a patient toolkit (see Table 1). Together, these tools and interventions are intended to enhance collaboration amongst primary healthcare professionals (physicians, nurses, nurse practitioners and community pharmacists) and between healthcare professionals and patients to enhance patient self management of blood pressure and improve the management and control of hypertension. The HMI beta phase also aims to determine and measure the effectiveness of the tools and improve best practice use of the current Canadian Hypertension Education Program (CHEP) recommendations [5] with a larger sample size of healthcare providers and patients than in the HMI Alpha phase. The HMI beta phase aims to measure the effectiveness of this initiative on a larger sample size by roughly quintupling the number of healthcare providers and patients.

**Table 1 T1:** Aspects of the HMI beta phase

• interactive, inter-professional education workshops, reflective exercises
• practice outreach and support to healthcare providers to support and assist in the integration of the tools and interventions in their practices
• inter-professional, evidence-informed healthcare provider toolkit that incorporates clinical reminders and prompts and practice audit feedback and aids inter-professional communication
• evidence-informed, leading edge patient toolkit that provides information and education and supports patient self-management.

The HMI Beta phase is a three-year initiative, which will end in 2010 to determine the effectiveness of the toolkits and interventions on the management and control of hypertension.

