**Sustainability of the Hypertension Management Initiative program**
◦ Development and usage of information management systems to improve and standardize high blood pressure patient care and treatment and to improve outcomes
◦ Statement of intention by participating healthcare providers to continue using key tools and learnings from the Hypertension Management Initiative.

**Improved hypertension management practices by healthcare providers participating in the Hypertension Management Initiative**
◦ Improved knowledge regarding best practices in management of patients with high blood pressure/hypertension
◦ Improved consistency with current CHEP recommendations in time elapsed from first high blood pressure reading to hypertension diagnosis
◦ Improved healthcare provider medication prescribing for hypertension patients consistent with current CHEP recommendations
◦ Improved assessment of medication adherence and side effects in high blood pressure/hypertension patient visits
◦ Improved assessment of global cardiovascular disease risk in patients with high blood pressure/hypertension
◦ Improved assessment of high blood pressure/hypertension patients' lifestyle risk factors and readiness to undertake lifestyle modifications
◦ Improved provision of support and advice to motivate high blood pressure/hypertension patients to make lifestyle recommendations
◦ Improved follow-up of high blood pressure/hypertension patients consistent with current CHEP recommendations
◦ Improved quantity and quality of inter-professional collaboration in management of patients with high blood pressure/hypertension.

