**Provider Toolkit**	1. Rx Dx Pads (with Diagnosis check off)	Communication tool for physicians to provide pharmacists diagnosis information with prescription allowing pharmacist to counsel patient appropriately and reinforce physician's messages regarding treatment adherence. It will be available in both paper and electronic form according to site preference.	Physician/Nurse Practitioner

	2. Proper Methods to Take Blood Pressure	A summary of directions for providers and patients on how to take blood pressure; includes step by step instructions for patients before and during BP measurements to ensure a correct BP reading.	

	3. Bp TRu 300	Automated office blood pressure measurement devices.	

	4. Blood Pressure Pocket Guide	An easy to use reference, pocket guide with Blood Pressure Risk chart/BMI calculator, waist circumference risk and stages of Change and counselling information to help your patients with their identified lifestyle modification. Patients also like the visual risk mapping format of the charts.	Provider

	5. HBP Flow Sheet & Assessment Form	Charting tool to record patient's progress with HBP care plan over time. This tool will remain in the patient's chart and will be used in paper version only in paper based sites. That form will be also faxed to an optical recognition site that will digitize the data and send it to a secure web-based custom data set. EMR (electronic medical record) sites will be sending the data directly to the same secure web based custom data set through a secure link.	Provider

	6. Confidential Provider Practice Audit Reports	Regular confidential practice reports are generated from the web-based data set and provided to the healthcare providers, namely physicians and nurse practitioners. The reports provide confidential, anonymous comparisons of one's practice to other participating healthcare providers and sites. The dataset is hosted on a PHIPA compliant server.	Physician/Nurse Practitioner

	7. RNAO-HSFO Nursing Best Practice Guideline, Nursing Management of Hypertension	A nursing best practice guideline collaboratively developed by the Registered Nurses' Association of Ontario and the Heart and Stroke Foundation of Ontario, with funding support from the Ontario Ministry of Health and Long-Term Care. This guideline has been endorsed by CHEP.	Nurses, Nurse Practitioners

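### For four provider indicators, the before-after comparison changes data source when the programme starts, so better recording cannot be told apart from better practice

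*Protocol article*

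**What the plan says.** All references are to the protocol article.

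- **Source by period.** Under Implementation of Toolkit and Interventions, the article specifies the data for measuring change across the two periods: "a combination of chart reviews, for the pre-program period, and the web-based patient dataset, for the program period, will be used". Providers' practice data and their patients' blood pressure data "will be used as their own comparators pre-intervention versus post-intervention".
- **What fills the programme dataset.** The same section describes a structured form completed at registration and then at follow-up: "A flow sheet form will continue to be used during the subsequent patient visits". Sites with electronic records use a purpose-built template screen instead.
- **The form is part of the intervention.** Table 6 lists the flow sheet in the provider toolkit as a "Charting tool to record patient's progress with HBP care plan over time". Table 1 describes the provider toolkit as a whole as a "healthcare provider toolkit that incorporates clinical reminders and prompts and practice audit feedback".
- **State of the earlier records.** On sites with electronic records: "Existing EMR systems at the sites are unable to systematically and fully capture". The sentence goes on to cover extracting and uploading the data that the project needs.
- **Outcomes.** Table 2 lists nine provider-practice indicators, among them "Improved assessment of medication adherence and side effects in high blood pressure/hypertension patient visits".
- **Timing.** Table 3 places practice-pattern measurement at Time 1 and Time 5 only, in both groups.

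**The concern.** The measuring instrument changes when the intervention starts. Before the programme, an assessment or a piece of advice counts only if a reviewer finds it in the routine chart. During the programme, it counts if it reaches a structured form or template that was not there before. If the new form captures a larger share of what clinicians do, the recorded rate rises with no change in what they do.

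At stake is whether a rise in these indicators can be reported as improved hypertension management, which is one of the evaluation's aims. The error is a bias, so enrolling more patients does not reduce it. It only makes a spurious difference more likely to reach statistical significance.

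**Working it through.** **1. Which indicators are exposed.** The nine provider-practice indicators in Table 2 sort as follows.

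| Group | Indicators | Count |
|---|---|---|
| Depend on an action being written down | adherence and side-effect assessment; global cardiovascular risk assessment; lifestyle and readiness assessment; support and advice | 4 |
| Rest on items likely to be recorded alike in both sources | time to diagnosis; prescribing; follow-up | 3 |
| Not evidently taken from charts | provider knowledge; inter-professional collaboration | 2 |

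**2. Whether anything in the article bridges the two sources.**
- The two extra data windows described for the Hawthorne effect both precede the workshop, so both fall in the chart-review period.
- Human validation of scanned forms checks transcription. It does not check agreement with charts.
- By Time 5 both groups have changed source and both have had the intervention. The delayed group therefore offers no comparison without the switch.
- No section describes chart review during the programme, or flow-sheet capture before it.

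**3. Formula.** Let t0 and t1 be the true rates of the action before and during the programme, and c0 and c1 the shares of actions recorded by chart and by flow sheet.

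Apparent change = t1·c1 − t0·c0 = (t1 − t0)·c1 + t0·(c1 − c0)

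The first term is practice and the second is recording. One observed difference cannot separate them. For example, a recorded rise from 48% to 57% fits two accounts:
- no change in practice: t = 0.60 in both periods, with 0.60 × 0.80 = 0.48 and 0.60 × 0.95 = 0.57;
- a true gain with equal recording: 0.48/0.95 = 50.5% rising to 0.57/0.95 = 60%.

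**4. Size when practice does not change.** The article gives none of the inputs, so these are assumptions: t = 0.60 and c1 = 0.95.

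| Charts record (c0) | 0.60 × (0.95 − c0) | Spurious gain |
|---|---|---|
| 95% | 0.60 × 0.00 | 0 points |
| 90% | 0.60 × 0.05 | 3 points |
| 80% | 0.60 × 0.15 | 9 points |
| 50% | 0.60 × 0.45 | 27 points |

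With c1 still at 95%, varying the true rate from 30% to 70% and chart recording from 60% to 90% gives 0.30 × 0.05 = 1.5 points at the least and 0.70 × 0.35 = 24.5 points at the most.

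**5. Chance that the artefact reaches p < 0.05.** This uses 337 per period, a figure the article derives for blood pressure and borrowed here only for scale. The periods are treated as independent samples, and clustering and pairing are ignored. With t = 0.50 and c0 = 0.75, the recorded rates are 0.375 and 0.475.
- Null standard error: √(2 × 0.425 × 0.575/337) = 0.0381.
- Alternative standard error: √((0.375 × 0.625 + 0.475 × 0.525)/337) = 0.0379.
- (0.100 − 1.96 × 0.0381)/0.0379 = 0.67, a probability of about 0.75.

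At the same true rate, the probability is about 0.10 if charts record 90% of actions and above 0.99 if they record 60%.

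The article states no figure for practice change, so there is none to reproduce.

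**The case against.** Several points on the other side stand.

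- **Scope.** A reader might infer that most provider indicators are biased. Step 1 shows that only four of the nine clearly depend on recording.
- **Certainty.** A reader might infer that the four indicators will rise whatever clinicians do. The article does not support that. It gives no chart completeness, and the artefact vanishes if both sources record equally. The form contents it names are blood pressure, body measures, lipids, lifestyle goals, the blood pressure goal and the chosen lifestyle factor. It does not say whether there are fields for adherence, side effects, global risk or readiness. An article may leave a field list to the full protocol. The mention of prompts in Table 1 describes the toolkit, not this form.
- **State of the electronic records.** The statement about existing systems concerns extraction and upload as well as capture. It is a reason to expect gaps, but it does not measure what a chart reviewer could find.
- **Real effect.** The prompts and the charting tool are intended parts of the intervention, so some of any rise may be true practice change.
- **Alpha phase.** It is tempting to set the pilot's gain in blood pressure measurement (27.8% to 45.7% of visits) beside these figures and call it artefact. The article does not say how either percentage was collected, and blood pressure measurement per visit is not a Table 2 indicator.
- **Main analyses.** The Abstract's comparisons, baseline against annual blood pressure and immediate against delayed wave, use BpTRU readings taken within the programme. This point does not reach them.

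These points narrow the concern without removing it. The change of source is a stated design choice, not a detail deferred to an analysis plan, and nothing described in the article bridges it.

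**Conclusion.** The concern holds in limited form. For the four recording-dependent indicators, the planned before-after change cannot separate better recording from better practice. The likely direction is towards apparent improvement, because a structured form introduced with the programme probably captures at least as much as routine charts.

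The size cannot be fixed from the article. On the assumed 60% true rate and 95% flow-sheet recording, it runs from 3 points with nearly complete charts to 27 points with charts that record half of the actions. It is zero if the two sources record equally. The documents do not support saying that any observed gain is artefact, only that the comparison cannot show that it is not. This is worth correcting because the remedy is cheap, but it does not threaten the main blood pressure results.

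**What to change.** Change the analysis wording in two places.

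1. Limit before-after claims about practice to items captured the same way in charts and in the programme dataset: drugs prescribed, visit dates and intervals, and recorded diagnosis.
2. Report the four recording-dependent indicators as descriptions within the programme period. If a before-after figure is still shown for any of them, state beside it that the change mixes recording with practice.

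Do not try to repair the comparison with a Time 5 chart abstraction that leaves out flow-sheet entries. The flow sheet becomes part of the chart and serves as the charting tool, so clinicians have little reason to write the same thing elsewhere. Excluding it would undercount practice during the programme and could hide a true improvement.

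**Cost:** no new data collection. The downside is that fewer indicators can carry a before-after claim.
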